### Statistical Analysis:

- Results will be expressed as mean  $\pm$  standard deviation or number (%). Comparison between categorical data will be performed using the Chi-square test. Comparison between different numerical data in the two studied groups will be performed using an unpaired t-test. Comparison between different times of measurements and baseline within the same group will be performed using repeated measure ANOVA. The SPSS computer program will be used for data analysis. P value less than 0.05 will be considered significant.

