### Labs Specific for the Study:

[figure not shown][figure not shown][figure not shown]

- Lactate
- CRP (C-reactive protein)
- Procalcitonin
- On days 1, 3, 7, 10, and 14.

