### **Application of APACHE II and SOFA Scoring Systems:**

- APACHE II score to be evaluated on study day 1.

- SOFA score to be evaluated on study day 1 and serially every day until ICU discharge or death or up to 28 days.

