### Statistical Analysis and Sample Size:

- Data entry, processing, and statistical analysis will be carried out using SPSS v29. Frequency tables with percentages will be used for categorical variables and descriptive statistics (mean  $\pm$  standard deviation or median with interquartile range) will be used for numerical variables. Tests of significance (Chi-square, student's t-test, or Mann Whitney's test) will be used according to the normality of the data. A P-value of less than 0.05 will be considered statistically significant. Total sample size 52 cases (organ dysfunction using SOFA score will be used as a primary outcome with proposed large effect size (0.8) and  $\alpha=0.05$  and power=0.80, so, 26 cases are needed in each group).

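### The only method named for serial measures is a within-arm comparison with baseline, which cannot show a fluoxetine effect, and the valid between-arm test leaves the recorded day-1 values unused

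*Protocol*

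**What the plan says.** Two sections of the Protocol describe the analysis.

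- **Statistical Analysis**, serial data: "Comparison between different times of measurements and baseline within the same group will be performed using repeated measure ANOVA". No arm term, arm-by-time term or other between-arm longitudinal method appears in either section. The section closes with a 0.05 significance threshold and does not confine the within-arm tests to description.
- **Statistical Analysis**, between arms: "Comparison between different numerical data in the two studied groups will be performed using an unpaired t-test".
- **Statistical Analysis and Sample Size**, between arms: "Tests of significance (Chi-square, student's t-test, or Mann Whitney's test) will be used according to the normality of the data". The threshold is the same: "A P-value of less than 0.05 will be considered statistically significant".

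Neither section includes a baseline covariate or says which day or summary of a repeated measure is compared between arms.

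Baseline values are nevertheless collected. Lactate, CRP and procalcitonin are measured as follows: "On days 1, 3, 7, 10, and 14". For severity: "APACHE II score to be evaluated on study day 1". SOFA is also scored on day 1 and then daily, ending when the patient leaves the ICU, dies or reaches day 28.

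SOFA is an efficacy measure. The outcome list places organ dysfunction among the secondary outcomes, while the sample-size paragraph says "organ dysfunction using SOFA score will be used as a primary outcome with proposed large effect size (0.8" and concludes "power=0.80, so, 26 cases are needed in each group".

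**The concern.** A within-arm test asks whether patients in one arm changed over time. It does not ask whether they changed more than patients in the other arm. Both arms receive full conventional sepsis therapy, so both may improve whatever fluoxetine does. A significant fall in one arm beside a non-significant fall in the other can then arise from chance alone.

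Two further weaknesses follow from the methods chosen. Classical repeated-measures ANOVA needs a value at every time point, but the SOFA series is cut short by death or discharge. Complete series therefore come from patients selected by their course, and the result describes that subset. Between the arms, an unadjusted test gives up precision that the day-1 values would supply at almost no cost, in a trial planned for only 60 patients.

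**Working it through.** **Inputs from the Protocol.** Standardised difference 0.8, alpha 0.05, power 0.80 and 26 per arm (Statistical Analysis and Sample Size); 60 patients (Study Population), taken here as 30 per arm.

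**Inputs assumed.** The correlation ρ between the day-1 value and the later value is not given, so I use 0.3, 0.5 and 0.6. The share of patients without a complete series is not given either, so I use 20%, 40% and 50%.

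**1. The plan's own figure.** For a two-sample t-test with two-sided alpha 0.05, d = 0.8 and 80% power, the noncentral-t solution is 25.5, rounded up to 26 per arm. Power at 26 is 0.807. The stated size reproduces and belongs to an unadjusted t-test. (A one-sided normal approximation gives 20 and does not match.)

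**2. Within-arm tests when there is no treatment effect.** Let each arm's test have power p for the same true change. The arms are independent, so

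P(exactly one arm significant) = 2p(1 − p).

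- p = 0.5: 2 × 0.5 × 0.5 = 0.50
- p = 0.8: 2 × 0.8 × 0.2 = 0.32

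To place p on the scale of this trial, take a single paired comparison with 26 per arm and ρ = 0.5. The SD of the change is then √(2(1 − 0.5)) = 1 SD.

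| Equal improvement in both arms (SD) | Within-arm power | Exactly one arm significant |
|---|---|---|
| 0.2 | 0.165 | 28% |
| 0.3 | 0.313 | 43% |
| 0.4 | 0.500 | 50% |
| 0.5 | 0.688 | 43% |
| 0.6 | 0.836 | 27% |
| 0.8 | 0.975 | 5% |

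The problem is largest for moderate change and fades when both arms improve strongly.

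**3. Complete series.** If 20%, 40% or 50% lack a full series, 26 per arm becomes 26 × 0.8 = 20.8, 26 × 0.6 = 15.6 or 26 × 0.5 = 13 in the within-arm ANOVA. This count applies to that ANOVA and not to the t-test.

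**4. Using baseline between arms.** ANCOVA multiplies the residual variance by 1 − ρ², so the effective standardised difference is 0.8/√(1 − ρ²). The figures ignore the one degree of freedom spent on the covariate.

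| ρ | 1 − ρ² | Effective d | n per arm for 80% power | Power at 26 per arm | Power at 30 per arm |
|---|---|---|---|---|---|
| none (t-test) | 1.00 | 0.80 | 26 | 0.807 | 0.861 |
| 0.3 | 0.91 | 0.84 | 24 | 0.843 | 0.891 |
| 0.5 | 0.75 | 0.92 | 20 | 0.904 | 0.940 |
| 0.6 | 0.64 | 1.00 | 17 | 0.942 | 0.968 |

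If the true difference is 0.5 instead of 0.8, power at 26 per arm is 0.424 for the t-test and 0.458, 0.533 or 0.599 for ANCOVA at the same three correlations.

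**5. Whether a mixed model can be fitted.** Daily SOFA from day 2 to day 28 gives 27 post-baseline days. An unstructured covariance then has 27 × 28/2 = 378 parameters, which 60 patients cannot support. The laboratory markers have four post-baseline days and 4 × 5/2 = 10 parameters.

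**The case against.** The best defence is that the Protocol does compare the arms. The sentence before the repeated-measures one specifies an unpaired t-test between the groups, and the other statistics section adds Mann-Whitney and chi-square. Under randomisation, omitting a covariate costs precision but does not bias the comparison, and the t-test meets its stated power. This stands, and it rules out three stronger readings.

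- A reader might infer that the analysis as a whole gives no estimate of the treatment effect. That is true of the within-arm ANOVA only.
- A reader might infer that significance in one arm alone will be taken as evidence of efficacy. The Protocol never says so. The 50% and 32% show what such a reading would risk, not what the plan announces. What remains is that this ANOVA is the only longitudinal method named and carries a significance threshold.
- A reader might infer that patients who die or leave the ICU are dropped from the randomised comparison. No exclusion rule is written. The loss follows from the classical ANOVA and falls on the within-arm result. A missing-data rule may properly sit in a statistical analysis plan, so its absence here is not the finding.

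The size of the gain from adjustment also rests on a correlation the Protocol does not give, and at 0.3 it is small. The argument does not apply to ICU mortality. For vasopressor dose, which the outcome list calls primary, no day-1 dose is explicitly scheduled. These limits narrow the point but leave it standing for SOFA and the laboratory markers.

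**Conclusion.** The point holds in limited form. The only method named for serial measures works within each arm and cannot show a fluoxetine effect. With equal true change, it would separate the arms by significance alone in 50% of trials at 50% within-arm power and in 32% at 80%. In its classical form it also rests on complete series, which death and ICU discharge cut short for SOFA.

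The between-arm t-test is valid but less precise than it could be. For SOFA and the laboratory markers, adjusting for the day-1 value would raise power from 81% to 84%, 90% or 94% (d = 0.8, 26 per arm) if the correlation is 0.3, 0.5 or 0.6. Those correlations are assumptions. The gain also requires a day-1 value that precedes treatment, which the Protocol does not state.

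**What to change.** 1. Label within-arm changes from baseline as descriptive only.
2. For SOFA and for lactate, CRP and procalcitonin, make the treatment estimate a between-arm ANCOVA at one day named in advance. Use the day-1 value of the same variable as covariate and state that it is taken before the first dose. APACHE II may be added as a second covariate.
3. For the laboratory markers (days 3, 7, 10 and 14), a mixed model with arm, day, arm-by-day and baseline may be used instead. Do not use an unstructured covariance for daily SOFA.
4. State how patients who die or leave the ICU before the named day enter the comparison. A mixed model does not settle this by itself, because it treats values after death as merely unobserved.
5. Do not extend the adjustment to ICU mortality, or to vasopressor dose unless a baseline dose is recorded.

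The cost is a change of analysis wording, the choice of a day and a rule for deaths and discharges, slightly more programming, and one degree of freedom per covariate. No extra patients or laboratory measurements are needed, provided that the day-1 values are taken before the first dose.
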